# Acupuncture treatment on the motor area of the scalp for motor dysfunction in children with cerebral palsy: study protocol for a multicenter randomized controlled trial

**DOI:** 10.1186/s13063-019-3986-z

**Published:** 2020-01-06

**Keywords:** Children with cerebral palsy, Motor dysfunction, Scalp acupuncture, Study protocol

## Abstract

**Background:**

Scalp acupuncture has been widely used as treatment for motor dysfunction in children with cerebral palsy in China. Previous studies have failed to provide high-quality evidence to demonstrate the effectiveness of this treatment in children with cerebral palsy. No high-quality randomized controlled trials on scalp acupuncture have been published. The aim of this study is to evaluate the effectiveness of Jiao’s scalp acupuncture when combined with routine rehabilitation treatment versus routine rehabilitation treatment alone for motor dysfunction in children with cerebral palsy.

**Methods/Design:**

This is a four-centre randomized controlled trial. One hundred cerebral palsy patients with motor dysfunction were enrolled. Patients will be allocated in a 1:1 ratio into either an acupuncture treatment group or a control group. Cerebral palsy patients in the control group will receive conventional rehabilitation treatment, whereas patients in the acupuncture group will receive a combination of scalp acupuncture and conventional rehabilitation treatment. Thirty-six treatment sessions will be performed over a 12-week period. The Gross Motor Function Measure and the Fine Motor Function Measure Scale will be assessed as the primary outcome measures. The Paediatric Evaluation of Disability Inventory and the Cerebral Palsy Quality of Life Questionnaire for Children will be selected as secondary outcome measures. All assessments will be conducted at baseline, week 4 (treatment 12), week 8 (treatment 24), week 12 (treatment 36) and week 24 (follow-up).

**Discussion:**

This is the first trial evaluating the efficacy and safety of scalp acupuncture as a treatment for motor dysfunction in children with cerebral palsy. The results of this trial are expected to provide relevant evidence demonstrating that scalp acupuncture can be used as an effective rehabilitation treatment method for improving motor dysfunction in children with cerebral palsy.

**Trial registration:**

ClinicalTrials.gov, NCT03921281. Registered on 19 April 2019.

## Background

Cerebral palsy (CP) is a well-recognized neurodevelopmental disorder beginning in early childhood and persisting throughout the patient’s lifetime. Motor disorders are often accompanied by disturbances in sensation, cognition, communication, perception, behaviour and seizures [1–3]. CP is the most common physical disability in childhood, with a prevalence of 1.5 to 3.8 per 1000 live births in Europe, Australia and the United States [4–6]. The latest research on medical conditions, healthcare resource utilization and healthcare costs in the USA showed that standardized reimbursement costs were higher for adults with CP compared to adults without CP by a total of $16,288 in 2016 [7]. In China, 2.48 per 1000 children aged 1 to 6 years of age were affected by CP based on a survey of 12 cities. According to this estimate, approximately 5 million children with CP are among children under 14 years of age, and approximately 40,000 new cases will be diagnosed every year based on the estimated number of 16 million new-borns per year in China [8]. Due to the motor dysfunction present, children with CP show restricted activities of daily living (ADL) and social participation, which greatly influence the quality of life (QOL) and their ability to adapt to society. In addition, this places a heavy burden on families and society as a whole and becomes a significant public health issue [9].

Conventional treatment for children with CP in the West is made up of multi-professional rehabilitation, including physical therapy (PT), occupational therapy (OT) and speech therapy (ST) [10, 11]. This method is complex, and the multi-disciplinary approach is designed to minimize complications and improve the child’s function [10]. In China, acupuncture has been widely used as a treatment for children with CP in combination with the standard conventional treatment, showing promising effectiveness in improving clinical symptoms [12–16], such as drooling, sleep, bowel function, spasm, motor function and daily life activities. However, high-quality evidence to support this method as an effective treatment for children with CP is lacking [17, 18].

Many different approaches with scalp acupuncture have been used to treat motor dysfunction in children with CP in China. These include approaches such as Jiao’s, Lin’s, Jin’s, Tang’s and the China scalp-point program of the international standardization [19, 20]. However, the motor area of Jiao’s scalp acupuncture is usually the region of choice in scalp acupuncture for the treatment of motor dysfunction in CP. Jiao’s scalp acupuncture combines a modern understanding of neuroanatomy and neurophysiology with traditional techniques of Chinese acupuncture to develop a radical new tool for affecting the functions of the central nervous system and accepts a central theory that incorporates brain functions into Chinese medicine principles [10]. The motor area of Jiao’s scalp acupuncture specifically used for the treatment of motor dysfunction in CP is the equivalent of the precentral gyrus of the cerebral cortex used for scalp projection [18]. However, the exclusive effectiveness of the motor area of Jiao’s scalp acupuncture treatment on motor dysfunction in children with CP is not well documented.

Therefore, our aim is to conduct a randomized controlled trial to evaluate whether stimulation of the motor area of Jiao’s scalp acupuncture is effective in improving motor function in children with CP.

## Methods/Design

### Objectives

The objective of this proposed study is to investigate whether scalp acupuncture treatment could significantly improve motor function in children with CP.

### Study design

This is an outcome assessor and data analyst-blinded, randomized, controlled superiority trial. The study is planned to be conducted from 1 January 2019 to 31 December 2021 in the Children’s Hospital of Fudan University. CP patients with motor dysfunction meeting the inclusion criteria will be allocated in a 1:1 ratio into either an acupuncture treatment group or a control group. CP patients in the control group will receive routine rehabilitation treatment, while the acupuncture group will receive a combination of routine rehabilitation treatment and scalp acupuncture. The Gross Motor Function Measure (GMFM) and the Fine Motor Function Measure (FMFM) will be assessed as primary outcome measures. The Paediatric Evaluation of Disability Inventory (PEDI) and the CP-Specific Quality of Life Scale (CP-QOL) will be selected as secondary outcome measurements. All assessments will be conducted at baseline, week 4 (treatment 12), week 8 (treatment 24), week 12 (treatment 36) and week 24 (follow-up). Figure 1 summarizes the flow of the entire trial. Figure 2 shows the study timeline, according to the Standard Protocol Items: Recommendations for Interventional Trials (SPIRIT) diagram. Additional file 1 presents the SPIRIT checklist.

**Fig. 1 Fig1:**
[figure not shown]
Route diagram of study design: Consolidated Standards of Reporting Trials (CONSORT) flow diagram showing subject allocation to the study conditions. *TG* treatment group, *CG* control group, *GMFM* Gross Motor Function Measure, *FMFM* Fine Motor Function Measure, *PEDI* Pediatric Evaluation of Disability Inventory, *CP-QOL* Cerebral Palsy Quality of Life

**Fig. 2 Fig2:**
[figure not shown]
Study timeline according to the Standard Protocol Items: Recommendations for Interventional Trials (SPIRIT) diagram

### Inclusion criteria

Participants meeting the following inclusion criteria will be included: (1) cerebral palsy patients between 12 and 72 months old, (2) cerebral palsy was diagnosed according to the diagnostic criteria of CP found in international guidelines, (3) cerebral palsy is the spastic type, and (4) voluntary participation and informed consent signed.

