### Randomization and allocation concealment

The recruited patients will be randomly assigned to either the experimental group or the control group according to a randomization and allocation plan. This allocation will be done using a computer-generated, block randomization (block size of 4 and 1:1 allocation) prepared by an independent epidemiologist not otherwise involved in the trial. A computer-generated block randomization process designed by the CTU is used to allocate participants to the treatment group or the control group in a 1:1 ratio (block size = 4). The randomization list is kept strictly confidential. Allocation concealment is ensured with the use of sequentially numbered (block number and sequence number), identical, opaque, sealed envelopes. Computerized randomization preserves allocation concealment and reduces the possibility of selection bias since the research assistant is kept unaware of the group assignments until after the participants are allocated to groups.

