### Statistical analysis

The Statistical Product and Service Solutions (SPSS) statistical package program (version 20.0, SPSS Inc., Chicago, Ill., USA) will be used to analyse data in the CTU of Children’s Hospital affiliated with Fudan University by statisticians. All analyses, including those from any participants who drop out during the trial, will be based on the intention-to-treat (ITT) principle using the last observation carried forward rule. Missing values will be handled by the mixed model for repeated measurements. Baseline information will be collected before randomization and includes the gender and age of patients, disease course, clinical type, GMFCS level, primary outcome (GMFM, FMFM) and secondary outcomes (PEDI, CP-QOL). Descriptive statistics will be used to detail baseline participant demographics and the general status of patients, such as gender, age, disease course, clinical type and GMFCS level. Variables will be checked for normal distribution and presented as mean +/− the standard deviation and compared by Student *t* test when normally distributed. For variables not normally distributed, the data will be expressed as median +/− the interquartile range, and non-parametric tests will be used. Categorical variables will be expressed as number (%) and analysed by *χ*^2^ tests or Fisher’s exact tests, when appropriate. The mixed effect model will be used to analyse the between-group difference in repeated measures for the two primary outcomes and other outcomes (GMFM, FMFM, PEDI and CP-QOL scores) across five testing time points (weeks 0, 4, 8, 12 and 24). Mean group difference and 95% confidence intervals will be reported. Safety analyses will be compared with the incidence of AEs in the two groups using the *χ*^2^ test. A *p* value of < 0.025 will be considered as statistically significant for the two primary outcomes.

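### The primary models name no adjustment for baseline age or GMFCS level in a broad CP population; prespecifying both would gain precision and protect the estimate against chance imbalance

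*Protocol article*

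**What the plan says.** The Inclusion criteria section of the Protocol article admits "cerebral palsy patients between 12 and 72 months old" and restricts the diagnosis to one form ("cerebral palsy is the spastic type"). Neither the inclusion nor the exclusion criteria limit GMFCS level, and the Scalp acupuncture treatment section provides for monoplegic through to quadriplegic children.

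The Randomization and allocation concealment section describes "block randomization (block size of 4 and 1:1 allocation) prepared by an independent epidemiologist". It gives block size, ratio, preparation and envelopes, and names no stratification factor.

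The Statistical analysis section lists gender, age, disease course, clinical type, GMFCS level and the outcome scores as information collected before randomisation. Their stated use is: "Descriptive statistics will be used to detail baseline participant demographics and the general status of patients, such as gender, age, disease course, clinical type", with GMFCS level next in that list. For efficacy, "The mixed effect model will be used to analyse the between-group difference in repeated measures for the two primary outcomes", over weeks 0, 4, 8, 12 and 24. No covariate is named.

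**The concern.** Cerebral palsy is described in the Background as a neurodevelopmental disorder of early childhood. It is plausible that motor gain over 12 weeks of routine rehabilitation depends on how old the child is and how severely affected. If so, two things follow from leaving age and GMFCS level out of both the allocation and the model.

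First, variation that could be explained goes into the residual, so the confidence interval is wider than it need be. Second, if the arms happen to differ in age or severity, that difference feeds directly into the estimated effect. Any adjustment chosen after the imbalance has been seen will then look selective.

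**Working it through.** **Inputs from the document** (Sample size calculation): difference in 12-week GMFM change 2.4, SD 3.0, alpha 0.025, power 0.9, 40 per group, 20% dropout, 50 per group randomised. No such figures are given for FMFM, so the arithmetic covers GMFM only.

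**Assumption**: R², the share of variance in 12-week GMFM change explained by age and GMFCS level together, is 0.1 to 0.3. The document gives no value.

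**1. The plan's own figure.** Two-sided normal approximation: n = 2 × (2.241 + 1.282)² × 3.0² / 2.4² = 38.8, so 39 per group against 40 stated. The exact t test at 40 per group gives power 0.899. Dropout: 40 / 0.8 = 50. The stated size is reproduced.

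**2. Gain from adjustment.** Unadjusted standard error at 40 per group: 3.0 × √(2/40) = 0.671. With adjustment the residual SD becomes 3.0 × √(1 − R²), so the standard error is multiplied by √(1 − R²).

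**3. Exposure to chance imbalance if unadjusted.** The imbalance contributes to the estimate with standard deviation √R² × 0.671; its 95% range is ±1.96 times that. The last two columns condition on a 2-SD imbalance (normal approximation).

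| R² | SE ratio | Adjusted power (t test) | 95% range of imbalance contribution | Type I error if it favours acupuncture | Power if it favours control |
|---|---|---|---|---|---|
| 0.1 | 0.949 | 0.929 | ±0.42 (17% of 2.4) | 0.046 | 0.77 |
| 0.2 | 0.894 | 0.955 | ±0.59 (24%) | 0.066 | 0.69 |
| 0.3 | 0.837 | 0.975 | ±0.72 (30%) | 0.085 | 0.61 |

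The standard error therefore falls by 5% to 16%.

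**4. Error rate over all randomisations.** Simulating the unadjusted t test with 40 per group gives a type I error of 0.0249 at R² = 0.3, and 0.0238 at an extreme R² = 0.5, against 0.025. The raised values in the table are conditional on an uncommon imbalance, and error rates below nominal when the arms are balanced offset them.

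**5. How often imbalance arises at 50 per arm.** If half the children are milder (assumption), two binomials (50, 0.5) differ by 8 or more children with probability 0.133 and by 6 or more with probability 0.271. If 12-week gain differs by 2-3 points between milder and severer children (assumption), 8 of 50 shifts the contrast by 0.16 × 2 = 0.32 to 0.16 × 3 = 0.48 points, or 13-20% of 2.4. If age is uniform over 12-72 months (assumption), its SD is 60/√12 = 17.3 months, the standard error of the difference in means is 17.3 × √(2/50) = 3.46, and a difference of 6 months or more has probability 0.083.

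**6. Cost of the extra parameters.** Step 2 ignores it. Age plus four indicators for five GMFCS levels is p = 5. With 80 children the variance is inflated by about 1 + p/(80 − p − 3) = 1 + 5/72 = 1.069. The SE ratio becomes √(0.9 × 1.069) = 0.98 at R² = 0.1 and √(0.7 × 1.069) = 0.87 at R² = 0.3, and power (73 degrees of freedom) about 0.91 and 0.97. The gain survives but is small at the low end. Entering GMFCS level as an ordered score (p = 2) costs only 1 + 2/75 = 1.027.

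**The case against.** The strongest reply has four parts.

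- **The model is not written out.** The article names no covariate but excludes none, and covariate lists are often left to an analysis plan. This stands: a reader might infer that adjustment is ruled out, but the text supports only that none is named. The missing stratification factor is firmer, because allocation is described in detail.
- **Chance imbalance is already part of sampling error.** This stands too. A reader might infer that imbalance can pass for a treatment effect and so invalidates the test. It does not: the error rate averaged over randomisations is nominal. The 0.3-0.5 point shift in step 5 is 0.5-0.8 of the standard error at 50 per arm, 3.0 × √(2/50) = 0.60, and under the assumptions in step 3 an imbalance worth the full 2.4 points is practically impossible.
- **The trial is not short of power.** Correct. The unadjusted analysis reaches its 0.9 target. If the pilot sample had a similar mix of children, which is not stated, the SD of 3.0 already contains the spread due to age and severity. Adjustment adds to that target and repairs no shortfall.
- **Starting score is partly handled.** Week 0 is a modelled time point and the planning is on change. That deals with where each child starts, but not with a rate of gain that depends on age or GMFCS level.

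It is also tempting to state as fact that natural gain differs widely across this population. The article gives no figure for 12-week gain by age or GMFCS level, so that remains a plausible assumption.

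**Conclusion.** The point holds as one of precision and of protection for the single realised estimate. The unadjusted primary analysis as described is valid and meets its stated power. It leaves unused two baseline variables that are likely to be prognostic and are already collected.

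For an assumed R² of 0.1-0.3, adjustment lowers the standard error of the GMFM contrast by about 5-16% and lifts power at 40 per arm from 0.90 to about 0.93-0.98. Charging for five extra parameters reduces this to about 2-13% and 0.91-0.97. Without adjustment, the 95% range of the imbalance contribution is ±0.42 to ±0.72 points. All of these sizes rest on the assumed R². The direction of the argument also depends on no adjustment being specified in documents that are not shown.

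**What to change.** In the Statistical analysis section, add that the primary GMFM and FMFM mixed models include baseline age (continuous) and GMFCS level, each with its interaction with visit, and that this is fixed before any outcome data are examined by arm. State whether GMFCS level enters as categories or as an ordered score, since sparse levels make the categorical form more costly. If an analysis plan already specifies these covariates, state them in the article.

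The cost is one sentence and a few model parameters, with no new data collection.

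Stratifying the remaining randomisation list is not recommended. The Trial status section says that recruitment began on 1 March 2019, so it would mix two allocation schemes, with pre-numbered envelopes, within a trial of 100 children. Covariate adjustment captures most of the benefit without that disruption.

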### Exclusion criteria

Participants with any of the following exclusion criteria will be excluded: (1) visual, auditory and mental disorders affecting the rehabilitation assessment; (2) children with epilepsy who are uncontrolled with medication; (3) bleeding tendencies; (4) being overly sensitive to acupuncture; (5) use of muscle relaxants or herbal therapies during the study period; and (6) participation in another clinical trial.

### Informed consent

Prior to the study, the general study process will be explained by the trial coordinator to potential participants and their legal guardian. Participants and their legal guardian will be informed that participation in the trial is completely voluntary and that they can withdraw from the trial at any time. In the event of their withdrawal, study data collected on the participant will not be deleted and will be used in the final analyses. Participants will also be asked for permission for the research team to share relevant data with people from the Universities taking part in the research or from regulatory authorities, where relevant. This trial does not involve collecting biological specimens for storage. Written informed consent should be obtained from each participant and his/her legal guardian before the participant undergoes any interventions related to the study.

### Interventions

The study is a randomized clinical trial carried out in outpatient rehabilitation departments of four hospitals. A total of 100 children with CP will be recruited. The patients will be randomly assigned to two different groups: 1) the treatment group and 2) the control group. The treatment group (*n* = 50) will receive routine rehabilitation treatment combined with scalp acupuncture three times per week for 12 weeks, while the control group (n = 50) will receive routine rehabilitation treatment three times per week for 12 weeks. Both groups will be evaluated at baseline, week 4 (treatment 12), week 8 (treatment 24), week 12 (treatment 36) and week 24 (follow-up). Both groups will receive routine CP rehabilitation treatment over the course of the 12-week study period. The routine rehabilitation program was designed according to the Chinese CP rehabilitation treatment guidelines, which include physical therapy (PT) and occupational therapy (OT) for 3 days a week [21]. Chinese herbal medicine and Chinese patent drugs will be prohibited during the trial.

### Scalp acupuncture treatment

This acupuncture intervention complies with the Standards for Reporting Interventions in Clinical Trials of Acupuncture (STRICTA) guidelines. Moreover, all the acupuncturists will attend special training to achieve a sound understanding of the scalp acupuncture intervention program and to standardize the procedures performed by the different acupuncturists. The trial adheres to the STRICTA guidelines [22, 23].

The parameters for scalp acupuncture has as the primary acupoint the motor area of Jiao’s Scalp acupuncture and as the secondary acupoint *Si shencong* (EX-HN1), which are set as follows:
Scalp acupoint location: The motor area of Jiao’s Scalp acupuncture is over the anterior central convolution of the cerebral cortex. It is a line starting from a point (known as the upper point of the motor area) 0.5 cm posterior to the midpoint of the anterior-posterior midline of the head and stretching diagonally to the juncture between the eyebrow-occipital line and the anterior border of the corner of the temporal hairline, which is indistinct. A vertical line extends upwards from the middle point of the zygomatic arch to the eyebrow-occipital line, and the intersection of the two lines is the projection of the motor area. The motor area is divided into five equal parts: the upper 1/5 being the motor area of the lower limbs and the trunk, the middle two-fifths being the motor area of the upper limbs and the lower two-fifths representing the motor area of the face [10] (Fig. 3 shows the motor area of Jiao’s scalp acupuncture). The site of the acupuncture treatment is determined according to the type of cerebral palsy and is based on the limb(s) affected by motor dysfunction. The motor area on the opposite side of the affected limb is selected as the site of acupuncture treatment in monoplegic and hemiplegic CP, whereas both motor areas are selected as the site of acupuncture treatment in diplegic and quadriplegic CP.

**Fig. 3 Fig3:**
[figure not shown]
The motor area of Jiao’s scalp acupuncture

*Si shencong* (EX-HN1) is 1 *cun* from the Baihui acupoint (Governing vessel; GV20), with one in front of it, one behind it, one on its left and one on its right, for a total of four acupoints (Fig. 4 shows the *Si shencong*). The Baihui acupoint (GV20) is 5 *cun* posterior to the front of the anterior-posterior midline of the head.
(2)Acupuncture manipulation: Disposable stainless steel needles (size 0.3 mm × 40 mm) will be manually inserted at an approximately 15-degree angle to depths of 1.5 and 2.0 cm, along the upper point and middle point of the motor area on the scalp [10]. The acupuncture direction of the *Si shencong* (EX-HN1) acupoint is toward the Baihui (GV20) acupoint. For treating motor dysfunction, the needles will be rotated for at least 200 rpm for 1 min every 20 min for a total of 60 min. Scalp acupuncture treatment will be performed by an independent certified practitioner (acupuncturist) with 5 years of clinical experience [10].(3)Treatment course: The scalp acupuncture treatment will be implemented three times a week (once every other day), twelve times per treatment course, with each patient having three treatment courses in total.

